#### Secondary outcome measures

Secondary efficacy end points included carbon monoxide–confirmed CARs for weeks 9 to 12 (CAR 9–12 Wks) and 9 to 52 (CAR 9–52 Wks) and 7-day point prevalence of abstinence at weeks 12, 24, and 52. Smoking abstinence will be self-reported and validated by measurements of exhaled carbon monoxide levels with a calibrated handheld monitoring device (MicroCO, Vyare Medical, Inc.) during clinic visits. Additional outcomes of interest will be: [1] Compare varenicline to placebo for changes in body weight and/or waist circumference at weeks 12, 24, and 52; [2] Compare varenicline to placebo for changes of diabetic outcomes (fasting blood glucose, HbA1c, insulinemia, and albumin to creatinine ratio) at weeks 12, 24, and 52; and (3) Compare varenicline to placebo for changes in blood pressure (BP) and heart rate (HR) at weeks 12, 24, and 52;

#### Safety end points

A summary table will present the number of events (includes lab data), number of subjects and severity of adverse events (AEs), and serious adverse events (SAEs). Any events documented in the period from the point of treatment initiation until 1 week after randomized treatment has been discontinued (V14) will be considered as relevant to the analysis.

#### Additional measures

Given that a better understanding of predictors of smoking cessation can be useful in identifying potential quitters and likely relapsers and that little is known about these predictors in diabetics, the role of different predictors of abstinence at week 12, week 24, and week 52 will also be examined. The level of smoking reduction will be also assessed in the participants who cannot achieved continuous abstinence at 12, 24 and 52 week.

### Randomization and interventions

#### Allocation to study treatment

Patients will be randomly assigned to either varenicline or placebo in a 1:1 ratio by using a computer-generated, 3-block randomization scheme.

#### Formulation and packaging

Varenicline (0.5 mg tablets) and placebo will be supplied in blinded bottles according to the computerized assignment. The hospital pharmacy will be in charge of randomization and packaging of the bottles.

#### Drug administration

Treatment will begin after the baseline visit.

Participants randomly assigned to varenicline will be titrated to full dose within the first week (0.5 mg/day for 3 days, 0.5 mg twice daily for 4 days; then 1 mg twice daily for the following 11 weeks). The day of up-dosing will correspond with the planned target quit date (TQD), one or two days before visit 2 at Week 1. Dosing should occur with a glass of water and it is recommended that subjects eat prior to dosing. There must be at least 8 h between the morning and evening dosing. If not tolerated, the dose may be reduced temporarily or permanently to 0.5 mg twice daily. The placebo tablets will look the same as the varenicline tablets. Dose titrations and allowable adjustments will be the same for both agents.

#### Compliance

Subjects will return blister cards at each programmed visit and a dosage record will be registered. Diabetic smokers will be subjected to their usual care throughout the study.

#### Cessation counseling

Both treatment groups will receive the same smoking cessation counseling starting at baseline and throughout the whole duration of the study. One-on-one counseling will be provided for up to 10 min and, whenever possible, done by the same counselor throughout the study.

### Study visits

The study will consist of a total of 19 visits: a screening visit, a baseline visit (V1), 12 study visits during the 12-week treatment phase (V2 to V13, of which 4 will be telephone contact visits) followed by an additional 5 study visits during the 40-week follow-up phase (V14 to V18, of which 2 will be telephone contact visits) (Fig. 1). Activities carried out during study visits are detailed in Table 1.

**Table 1 Tab1:** Study schedule/flowchart

**Procedure**	Sc V0	BL V1	Wk 1 V2	Wk 2 V3	Wk 3 V4	Wk 4 V5	Wk 5 TC V6	Wk 6 V7	Wk 7 TC V8	Wk 8 V9	Wk 9 TC V10	Wk 10 V11	Wk 11 TC V12	Wk 12 V13	Wk 13 V14	Wk 24 V15	Wk 36 TC V16	Wk 44 TC V17	Wk 52 V18
Informed consent		X																	
Eligibility Criteria	X	X																	
Medical Hx	X	X																	
Antidiabetic drug use		X	X	X	X	X		X		X		X		X	X	X			X
Smoking Hx	X	X																	
Cigarette consumption	X	X	X	X	X	X	X	X	X	X	X	X	X	X	X	X	X	X	X
Exhaled CO		X	X	X	X	X		X		X		X		X	X	X			X
BP, HR	X	X	X	X	X	X		X		X		X		X	X	X			X
BMI, waist		X												X		X			X
Sociodemographics		X																	
Motivation to quit by VAS		X																	
FTCD		X																	
BDI & BAI		X																	
Self-Efficacy to quit by VAS		X																	
Cessation counseling		X	X	X	X	X	X	X	X	X	X	X	X	X	X	X	X	X	X
Adverse events		X	X	X	X	X		X		X		X		X					
Blood chemistry and CBC	X	X		X											X				
Urinalysis	X	X		X											X				
DM lab tests		X													X	X			X
Dispense study drug*		X	X	X	X	X		X		X		X							
Dosing record			X	X	X	X		X		X		X		X					

*Sc* screening, *BL* baseline, *TC* telephone contact, *CO* carbon monoxide, *HR* heart rate, *BP* blood pressure, *BMI* body mass index, *VAS* visual analog score, *FTCD* Fagerstrom Test for Cigarette Dependence, *BDI* beck depression inventory, *BAI* beck anxiety inventory, *QoL* quality of life, *CBC* complete blood count, *DM* diabetes mellitus

*Dispense study drug – a week supply of drug/placebo is dispensed at each visit with the exception of Wk 4, Wk 6, Wk 8 and Wk 10 when a whole 2 weeks supply is given

#### Screening visit

At screening, patients who expressed an interest to participate in the study, will be checked for eligibility by evaluating the criteria for inclusion and exclusion. Medical history, and smoking history will be noted. Physical examination will be performed. BP and HR will be measured. Blood and urine will be collected for standard clinical laboratory evaluations (including HbA1C). Qualified participants will be then invited to attend the Baseline visit.

#### Baseline visit (V1)

The Baseline Visit will be scheduled no less than 3 working days after screening so that laboratory results would be available for review. Patients with abnormal laboratory results judged to be clinically significant will not be considered for inclusion. Eligible patients are asked to go over the patient information sheet and to sign the consent form. General socio-demographic features, medical hx, drug prescriptions, smoking hx, and motivation to quit will be noted in the chronic renal failure (CRF). The following baseline assessments will be carried out: number of cigarette smoked/day, eCO levels, blood pressure, HR, BMI, waist circumference, and questionnaires (Fagerström Test for Cigarette Dependence (FTCD), Beck Depression Inventory (BDI), Beck Anxiety Inventory (BAI)). Blood and urine samples will be collected for standard clinical laboratory evaluations (including fasting blood glucose, HbA1C, insulinemia, and albumin to creatinine ratio). Any AEs will be noted in the CRF. Eligibility criteria will be reviewed again prior to randomization. Regardless of their assignment, all patients will receive smoking cessation counseling and instructed to set a TQD 1–3 days before the next study visit (visit 2 at Week 1). Patients will receive a full week supply of their assigned treatment prior to check-out (either varenicline or placebo depending on the study-arm allocation). Study drug will be dispensed according to the plan illustrated in Table1.

#### Treatment study visits 2 to 13

After V1, patients will return for their treatment phase visits (V2–V13). With the exclusion of Visits 6, 8, 10 and 12 (telephone contact visits), patients will return to attend weekly visits to the clinic over the following 12 weeks. Study visits will occur within 3 days of each scheduled visit date. Patients returning for their Week-1 visit (i.e. V2; TQD-visit) must have adhered to their TQD, abstaining from smoking for 1–3 days before the study visit. At each visit, patients will be reminded of the importance of staying cigarette free and will receive professional counseling for relapse prevention. Number of cigarette smoked/day, eCO levels, blood pressure, HR (BMI, and waist circumference only at Week-12 visit), and AEs will be noted in the CRF. Any unused study drug will be returned to the principal investigator. Patients will receive a supply of their assigned treatment prior to check-out according to the plan illustrated in Table1.

#### Follow-up study visits 14 to 18

Following completion of the treatment phase (V2–V13), patients will continue in the nontreatment follow-up phase of study. Only patients completing the week-12 visit will be eligible to continue in the nontreatment follow-up phase (V14–V18). With the exclusion of Visits 16 and 17 (telephone contact visits), patients will return for their study visits at week-13 (V14), week-24 (V15), and week-52 (V18). Number of cigarette smoked/day, eCO levels, BP and HR (BMI, and waist circumference only at week-24 and week-52 visits) will be noted in the CRF. Blood and urine samples will be collected for evaluation of fasting blood glucose, HbA1C, insulinemia, and albumin to creatinine ratio at week-24 and week-52 visits.

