#### Primary outcome measure

Consistent with previous varenicline randomized controlled trials (RCTs) [25–27] and the Society for Research on Nicotine and Tobacco recommendations [28], the primary efficacy end point is the carbon monoxide–confirmed (≤ 10 ppm) CAR from week 9 to week 24 (CAR 9–24 Wks). Smoking abstinence will be self-reported and validated by measurements of exhaled carbon monoxide levels with a calibrated handheld monitoring device (MicroCO, Vyare Medical, Inc.) during clinic visits.

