#### Methods of analyses

Baseline and demographic data will be listed for all treatment groups. Summary statistics will be provided for each treatment group. At baseline, differences between varenicline and placebo groups will be evaluated by means of one-way analysis of variance and Mann–Whitney *U*-test for normally and not normally distributed continuous variables, respectively; *χ*^2^ test will be used for categorical variables. The secondary endpoints will be analyzed using procedures similar to that described above for the primary endpoint. Intention-to-treat analysis will be adopted for efficacy evaluation, assuming that subjects lost to follow-up continued smoking.

Safety data will be summarized for both treatment groups and summary statistics provided.

Any events documented in the period from the point of treatment initiation until 1 week after randomized treatment has been discontinued (V14) will be considered as relevant to the safety analysis. AEs will be coded using MedDRA (Medical Dictionary for Regulatory Activities) and assigned grades based on NCI CTCAE (National Cancer Institute Common Terminology Criteria for Adverse Events). Between-groups comparisons for both individual and clustered AE rates will be carried out using χ^2^ testing or Fisher’s exact test, as appropriate.

Multiple logistic regression models will be built to identify independent predictors associated with CARs at week 12, week 24, and week 52.

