## Results

In total, 300 subjects have been randomized to the varenicline (*n* = 150) or placebo (*n* = 150) groups with 194 subjects completing the study at week 52; 100 in the varenicline group and 94 in the placebo group. The conduct phase of the study is completed, while data cleaning and analyses are ongoing.

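### Assessment after week 12 depends on attending the week-12 visit, which creates missing data by design and weakens the intention-to-treat aim, mainly for secondary outcomes

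*Protocol article*

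**What the plan says.** Participants are "randomly assigned to either varenicline or placebo in a 1:1 ratio" (Allocation to study treatment). Methods of analyses then states: "Intention-to-treat analysis will be adopted for efficacy evaluation, assuming that subjects lost to follow-up continued smoking".

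Follow-up study visits 14 to 18 sets the entry rule for everything after week 12: "Only patients completing the week-12 visit will be eligible to continue in the nontreatment follow-up phase". The condition is completion of the visit (V13). It is not completion of the drug course.

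Several endpoints need data from beyond that point. The primary endpoint is the CO-confirmed "CAR from week 9 to week 24". The secondary endpoints include CAR 9–52, "7-day point prevalence of abstinence at weeks 12, 24, and 52" and "changes in body weight and/or waist circumference at weeks 12, 24, and 52", with diabetic outcomes, blood pressure and heart rate at the same three time points.

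**The concern.** An intention-to-treat comparison rests on trying to observe the outcome in everyone randomised. Here the protocol stops trying for anyone who misses one visit twelve weeks after randomisation. Missing that visit may well be related to how treatment went, so the resulting gaps cannot be presumed unrelated to arm or outcome.

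Two kinds of endpoint are exposed:

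- **Point prevalence at weeks 24 and 52.** This does not require abstinence at earlier visits. Someone who misses V13 and is abstinent later could count as a success, but nobody is scheduled to look.
- **Continuous outcomes.** An assumption that a person went on smoking supplies no HbA1c, weight or blood pressure. These comparisons become comparisons among week-12 completers, a group selected after randomisation.

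**Working it through.** **1. What a participant who misses V13 loses, read from Table 1**

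| Outcome | Scheduled after baseline | Available if V13 is missed |
|---|---|---|
| Diabetes laboratory tests | Weeks 13, 24, 52 | None |
| BMI and waist | Weeks 12, 24, 52 | None |
| Blood pressure, heart rate | Treatment-phase clinic visits, then weeks 13, 24, 52 | Treatment-phase values up to week 10 only |
| 7-day point prevalence | Weeks 12, 24, 52 | None of the three |

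The section on clinical laboratory parameters confirms week 13 as the first post-baseline time for HbA1c, insulinemia and albumin-to-creatinine ratio. That visit (V14) lies behind the week-12 condition. Glucose is also part of the week-2 blood chemistry, but that is not one of the endpoint times.

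**2. Primary endpoint**

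Week 12 lies inside the week 9–24 window, and abstinence is confirmed by CO at clinic visits. A missed V13 therefore already leaves a gap in confirmation, whatever happens later. Only a participant who missed V13 but would still have been accepted as continuously abstinent is affected, so the added effect is probably small.

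**3. How many could be affected**

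The Results section gives "194 subjects completing the study at week 52", of whom 100 were on varenicline and 94 on placebo, from 150 randomised to each.

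- Total: 100 + 94 = 194, which agrees with the stated figure; 300 − 194 = 106, and 106/300 = 35.3%
- Varenicline: 150 − 100 = 50, and 50/150 = 33.3%
- Placebo: 150 − 94 = 56, and 56/150 = 37.3%
- Difference between arms: 37.3 − 33.3 = 4.0 points

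The number barred at week 12 is not given. The counts above are upper bounds, since they include people lost after week 12, to whom the rule did not apply.

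**4. Possible effect on point prevalence**

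Let b be the share barred in an arm and a the share of those who are in fact abstinent. Scoring them all as smokers lowers that arm's rate by b × a. The difference (varenicline minus placebo) changes by (b × a for placebo) − (b × a for varenicline). The documents give no value for a; 10–20% is an assumption.

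| Assumed a | Varenicline lowered by | Placebo lowered by | Change in difference |
|---|---|---|---|
| 10% in both arms | 0.333 × 10 = 3.3 points | 0.373 × 10 = 3.7 points | +0.4 point |
| 20% in both arms | 0.333 × 20 = 6.7 points | 0.373 × 20 = 7.5 points | +0.8 point |
| 20% varenicline, 0% placebo | 6.7 points | 0 | −6.7 points |
| 0% varenicline, 20% placebo | 0 | 7.5 points | +7.5 points |

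With equal abstinence among those barred, the shift slightly favours varenicline, so scoring missing as smoking is not automatically conservative. The last two rows mark the extremes; nothing in the document suggests that either applies. For scale, the sample size section plans for a difference of 18.7 points on CAR 9–24.

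**The case against.** **The two rules can both be carried out.** A reader might infer that the week-12 condition contradicts the intention-to-treat analysis. It does not: all 300 can be analysed in their assigned arms with missing counted as smoking. This stands, and the point is one of weakened follow-up.

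**Scoring as smokers is an inference.** The stated rule covers those lost to follow-up and does not name people whom the protocol itself stopped following. This also stands, but it does not help the plan. If the rule does not cover them, no stated rule does.

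**The condition is the visit.** A reader might infer that anyone who stops study drug early is dropped. The text does not say so; a participant who stops drug and attends V13 continues.

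**The week-1 visit.** A reader might see a second barrier in the wording that patients returning at V2 "must have adhered to their TQD". The protocol attaches no consequence to failing this. Additional measures plans to assess smoking reduction at weeks 12, 24 and 52 in those who do not achieve continuous abstinence, which presupposes that non-quitters are followed.

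**The size is uncertain.** Some early leavers could not have been reached under any rule, and the only documented imbalance between arms is 4.0 points at week 52. The calculation therefore gives a ceiling, not an estimate.

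**Sensitivity analyses usually sit in the SAP, which is not shown.** Their absence is indeed no finding. The follow-up rule itself is stated in the protocol, however, and no SAP can recover visits that were never scheduled.

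**Conclusion.** The point holds as a weakness in follow-up. By making later assessment conditional on a post-randomisation visit, the protocol creates avoidable missing data.

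The clearest harm is to the diabetes, weight and waist comparisons and to later blood pressure and heart rate. These are restricted to week-12 completers, and the smoking assumption cannot fill the gap. Point prevalence at weeks 24 and 52 is affected next. At the upper bound for the number barred, and with 10–20% of them assumed abstinent equally in both arms, arm rates are understated by about 3 to 7 points and the difference moves by about 0.4 to 0.8 point. It moves by more only if abstinence among those barred differs by arm. The effect on CAR 9–24 is probably small.

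The documents do not support a claim that the primary result is materially biased.

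**What to change.** **Protocol wording.** Replace the week-12 condition with: All randomised participants who have not withdrawn consent will be assessed at weeks 13, 24, 36, 44 and 52, whether or not they attended the week-12 visit.

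**For this trial.** The Results section says conduct is complete while data cleaning and analysis continue, so the missed visits cannot be recovered. The following can still be done:

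1. Use any smoking status or measurement recorded after a missed V13.
2. Report by arm how many participants were excluded by the week-12 rule, separately from withdrawal and loss to follow-up.
3. State how these participants are handled for each endpoint, and add a multiple-imputation or tipping-point sensitivity analysis that does not assume they smoked.
4. Label the diabetes, weight and waist, blood pressure and heart rate results after week 12 as conditional on completing week 12.

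**Cost.** One sentence of protocol text and a modest amount of extra analysis and reporting. In a trial still recruiting there would also be a few more contacts, and early leavers are harder to reach, so some data would still be missing.

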### Study assessments

Besides lab tests (for blood chemistry—including sodium, potassium, chloride, BUN, creatinine, glucose, SGOT, SGPT, LDH, alkaline phosphatase, total bilirubin, total cholesterol, HDL, LDL triglycerides, complete blood count—urinalysis, and T2DM specific lab tests—including fasting glucose, HbA1c, insulinemia, and albumin to creatinine ratio), the following assessments will be performed throughout the study:

#### Exhaled carbon monoxide monitoring

Participants’ smoking status will be objectively verified by measurements of exhaled carbon monoxide levels with a calibrated handheld monitoring device (MicroCO, Vyare Medical, Inc.). Levels of CO in the exhaled breath of a regular smoker (eCO) are generally ≥ 10 ppm. Participants will not be allowed to smoke within 30 min prior to eCO level measurements.

#### Office BP and HR measurements

Systolic (SBP) and diastolic BP (DBP) measurements will be conducted according to the recommendations of the Seventh Report of the Joint National Committee on Prevention, Detection, Evaluation, and Treatment of High Blood Pressure [29]. After a 5-min rest, BP and HR measurements will be obtained by a semi-automated oscillometric sphygmomanometer (Smart Pressure, CA-MI Snc, Parma, Italy). Two measurements in the sitting position, spaced 1–2 min apart, will be obtained. Measurements will be taken late in the morning, and participants asked not to smoke or consume caffeinated drinks for at least 30 min prior to each visit. The average of two measurements will be considered for analysis.

#### BMI and waist circumference

Participants will remove shoes and heavy clothing and will be weighed using a mechanical column scale (Seca, Intermed Srl, San Giuliano Milanese, Italia). Height measurements will be taken by using a standing scale slide bar. BMI will be computed as weight/height^2^ (kg/m^2^). To correctly measure waist circumference, place a tape measure just above the hipbones, then bring the tape measure all the way around the body until leveling to the belly button. Make sure tape measure is not too tight and that it's straight, even at the back. Check the number on the tape measure right after breathing out.

#### Fagerström test for cigarette dependence (FTCD)

Cigarette dependence will be assessed via a FCTD questionnaire [30]. The questionnaire consists of 6 questions which will be answered by the participant himself/herself. The scores obtained on the test allow to classify nicotine dependence into 3 levels: Mild (0–3 points), moderate (4–6 points), and severe (7–10 points).

#### Beck depression inventory

Subjective ratings of depression will be assessed with Beck Depression Inventory–II (BDI-II) [31]. The BDI-II is a 21-item, self-report rating inventory that measures characteristic attitudes and symptoms of depression. Internal consistency for the BDI-II ranges from 0.73 to 0.92 with a mean of 0.86. The BDI-II demonstrates high internal consistency, with alpha coefficients of 0.86 and 0.81 for psychiatric and non-psychiatric populations, respectively. Scores from 0 through 9 indicate no or minimal depression; scores from 10 through 18 indicate mild to moderate depression; scores from 19 through 29 indicate moderate to severe depression.

#### Beck anxiety inventory

Subjective ratings of anxiety will be assessed with Beck Anxiety Inventory (BAI) [32]. The BAI evaluates physiological and cognitive symptoms of anxiety. Each of the 21 BAI items is descriptive of a symptom of anxiety and is rated on a scale of 0 to 3. The BAI can be administered verbally by a trained interviewer or can be self-administered. The BAI has been found to discriminate well between anxious and non-anxious diagnostic groups and, as a result, is useful as a screening measure for anxiety in a variety of clinical populations. It has an average reliability coefficient of 0.92 and a test–retest reliability of 0.75. Scores from 0 through 7 is interpreted as a "Minimal" level of anxiety; 8–15 as "Mild"; 16–25 as "Moderate", and; 26–63 as "Severe".

